### Study outcomes

#### Primary outcomes

The primary efficacy outcome is the incidence of symptomatic VTE within 90 days following surgery. Symptomatic VTE is defined according to the International Society on Thrombosis and Haemostatis (ISTH) criteria.^22^ DVT is objectively confirmed by the presence of thrombotic material in the lumen of one or more deep veins of the leg. PE is objectively confirmed by the presence of thrombotic material in the lumen of a pulmonary vein.

The primary safety outcome is the incidence of major bleeding within 90 days following surgery. Bleeding is defined as major if it fulfils one of the ISTH criteria listed below, as described by Schulman *et al*^23^:

Fatal bleeding; and/orBleeding that is symptomatic and occurs in a critical area or organ, such as intracranial, intraspinal, intraocular, retroperitoneal, pericardial, a non‐operated joint or intramuscular with compartment syndrome, assessed in consultation with the surgeon; and/orExtrasurgical site bleeding causing a fall in haemoglobin level of 20 g/L (1.24 mmol/L) or more, or leading to transfusion of two or more units of whole blood or red cells, with a temporal association within 24–48 hours of the bleeding and/orSurgical site bleeding that requires a second intervention—open, arthroscopic or endovascular.Surgical site bleeding that is unexpected and prolonged and/or sufficiently large to cause haemodynamic instability. There should be an associated fall in haemoglobin level of at least 20 g/L (1.24 mmol/L) or transfusion, indicated by the bleeding, of at least two units of whole blood or red cells, with temporal association within 24 hours of the bleeding.

#### Secondary outcomes

CRNMB: any non-major bleeding requiring medical intervention by a healthcare professional, and/or leading to hospitalisation or an increased level of care and/or prompting a face-to-face evaluation.Prosthetic joint infection (PJI), defined according to the European Bone and Joint Society, as described by McNally *et al.*^24^Myocardial infarction, ischaemic stroke and death.Patient-reported outcome measures (EQ-5D (EuroQol 5-Dimension Quality of Life Questionnaire), Oxford Hip Score,^25^ Oxford Knee Score,^26^ Visual Analogue Scale (VAS) pain).Impact of events on quality-adjusted life years (QALYs) and societal costs.

### Study follow-up

Primary and secondary outcomes will be assessed using a questionnaire at 2 weeks, 6 weeks and 90 days postoperatively. Additionally, patients who experience a symptomatic VTE, major bleed or PJI receive an additional questionnaire at 1 year postoperatively. Controls, 1:1 matched on age, sex, study centre and type of surgery, will receive the same questionnaire. All postoperative care is according to the current standard of care; no routine VTE screening will be performed. In the case of a (possible) outcome event, additional data on the event, including imaging studies, consult letters, discharge letters and any other relevant information, are collected from the medical record of the participant. In table 1, study procedures and assessments are presented.

**Table 1 T1:** An overview of study procedures and assessments

Evaluation	Preoperative	Day 0 (surgery)	2 weeks	6 weeks	90 days	12 months
Baseline characteristics, including age, sex, BMI, comorbidities and VTE risk factors	X					
Perioperative outcomes*		X				
Outcome event(s) by questionnaire			X	X	X	
Treatment compliance (questionnaire)				X		
VAS	X				X	
OHS/OKS	X					
EQ-5D	X				X	
In case of an outcome event(s) and controls						
OHS/OKS						X
SF-36						X
EQ-5D						X

* Perioperative variables are derived from the Dutch Arthroplasty Registry (LROI).

BMI, body mass index; EQ-5D, EuroQol 5-Dimensions Quality of Life Questionnaire; LROI, Landelijke Registratie Orthopedische Interventies; OHS, Oxford Hip Score; OKS, Oxford Knee Score; SF-36, 36-Item Short Form Survey; VAS, Visual Analogue Scale; VTE, venous thromboembolism.

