### Study design

The DISTINCT trial is a national, multicentre, randomised, multiarm, open-label trial with blinded outcome adjudication. Patients will be recruited from teaching hospitals, general hospitals and private clinics across the Netherlands.

The study will consist of three study arms (figure 1) to which patients will be allocated based on their predicted VTE risk, as calculated by the TRiP(plasty) score (figure 2).^18^ Patients will either be assigned to the low VTE risk study arm: DISTINCT-1 trial (predicted 90-day postoperative VTE risk <1%), the intermediate VTE risk study arm: DISTINCT-2 study (predicted VTE risk ≥1% and ≤1.5%) or the high VTE risk study arm: DISTINCT-3 trial (predicted VTE risk >1.5%). Patients in the DISTINCT-1 trial will be randomised to either short-duration thromboprophylaxis (in-hospital only) or the control treatment (standard thromboprophylaxis). This study arm will be analysed as a non-inferiority trial. In the DISTINCT-2 study, participants will be treated with standard thromboprophylaxis. This study arm will be observational. Participants in the DISTINCT-3 trial will be randomised between the intervention (higher dose and longer duration thromboprophylaxis) and the control treatment (standard thromboprophylaxis). This study arm will be analysed as a superiority trial. All primary outcomes will be assessed up to 90 days following surgery. During the study, trial outcomes will be regularly evaluated by an independent Data and Safety Monitoring Board (DSMB). The Standard Protocol Items: Recommendations for Interventional Trials guidelines were followed when drafting the study protocol.^19 20^

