### Sample size

#### Sample size calculation: DISTINCT-1 trial

By only including patients with a predicted VTE risk of <1.0%, a 3-month cumulative incidence of symptomatic VTE of 0.75% is expected in the control arm. This risk is based on the results from the development and validation studies of the TRiP(plasty) score.^18^ Multiple observational studies among patients in fast-track treatment protocols have shown that the risk of postoperative symptomatic VTE is ≤1% or even <0.5% with the use of in-hospital thromboprophylaxis only.^6 8 10 11^ Therefore, we expect no reduced or increased VTE risk when thromboprophylaxis is limited to in-hospital use only. Hence, the expected risk in the short-duration prophylaxis group is also 0.75%. The non-inferiority limit is set at 1%, which represents the minimal clinically important difference.^27^ Considering a one-sided alpha of 0.025 and a power of 90%, this leads to a necessary sample size of 3130 patients. To account for a maximum dropout rate of 10%, we aim to include 1739 patients in each group, totalling 3478 patients.

The incidence of (any) bleeding following THA/TKA has been reported to range from 0.5% to 3%. This variation is mainly caused by differences in bleeding definitions and the completeness and accuracy of patient follow-up.^12 13^ Hence, exact estimations of bleeding risks are difficult to obtain. Based on the available literature, we estimate that shortening the duration of thromboprophylaxis has no effect on major bleeding rates. The estimated relative reduced risk for minor bleeding+CRNMB is approximately 29%–50%.^10^,^1228 29^

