### Analysis of secondary endpoints

Risks of CRNMB, minor bleeding, PJI, myocardial infarction, ischaemic stroke and death will be estimated and compared between groups in a similar fashion. Functional and quality-of-life outcomes at 1 year postoperatively in patients who experienced symptomatic VTE, major bleeding or PJI and in controls will be compared between groups, across all groups.

We expect that the intervention will improve health outcomes at lower healthcare and societal costs. A cost-utility analysis will be performed using a Markov model to estimate the lifelong impact of VTE and bleeding events on discounted QALYs and societal costs. The intervention group will be compared with the control group according to ITT, separately for the DISTINCT-1 trial and the DISTINCT-3 trial.

The 3-month symptomatic VTE and bleeding rates (from the primary analysis) will be estimated from the trial. The impact per event on QALYs (ie, estimated using the EQ-5D), as well as on healthcare and productivity costs, will be estimated from the differences in patient-reported questionnaires preoperatively and after 14 days, 30 days, 90 days and 12 months. Medication and other healthcare will be valued using Dutch reference prices. QALYs and costs will be compared using net-benefit analysis, taking data and parameter uncertainty into account and with multiple imputation to account for missing data. Sensitivity and scenario analyses will include perspective (societal vs healthcare) and the valuation of productivity (friction costs vs human capital approach).^33^

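### The 1-year controls are not matched on DISTINCT study or predicted VTE risk, so the pooled 1-year comparison of function and quality of life is likely confounded by risk profile

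*Protocol article*

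**What the plan says.** Four statements in the protocol article bear on this.

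- **Cases.** Under Study follow-up, "patients who experience a symptomatic VTE, major bleed or PJI receive an additional questionnaire at 1 year postoperatively".
- **Controls.** The same section continues: "Controls, 1:1 matched on age, sex, study centre and type of surgery, will receive the same questionnaire". Predicted risk, DISTINCT study, BMI, comorbidity and preoperative scores are not in that list.
- **Comparison.** Under Analysis of secondary endpoints, 1-year function and quality of life "in patients who experienced symptomatic VTE, major bleeding or PJI and in controls will be compared between groups, across all groups". I read this as cases against controls, pooled over the three studies. No adjustment is named.
- **Impact per event.** Later in that section, the effect of an event on QALYs and costs "will be estimated from the differences in patient-reported questionnaires preoperatively and after 14 days, 30 days, 90 days and 12 months". This estimate feeds the Markov model.

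Two further facts matter. Under Study design, "patients will be allocated based on their predicted VTE risk, as calculated by the TRiP(plasty) score", so the study a patient is in is itself a band of predicted event risk. Table 1 marks EQ-5D and OHS/OKS before surgery for everyone, along with BMI, comorbidities and VTE risk factors. It marks SF-36 at 12 months only, for cases and controls.

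**The concern.** Patients who have a VTE will tend to be those the score predicted would have one. The legend of the TRiP(plasty) figure mentions BMI, myocardial infarction and TIA. The Introduction puts VTE risk after surgery at 5% to 10% in patients with a previous VTE, and says VTE itself is associated with lost quality of life. Such patients may well score lower at 1 year without any new event. Controls drawn without regard to predicted risk will include more low-risk patients than the cases do, and part of the difference would then be credited to the event. The likely direction is to overstate its harm.

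The choice of controls is also a data-collection rule. Only cases and selected controls receive the 12-month OHS/OKS, SF-36 and EQ-5D. Regression can adjust later, but it cannot supply questionnaires from high-risk controls who were never asked. Enrolment began in November 2024, so the first 12-month questionnaires fall due from about November 2025.

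At stake are a secondary outcome and, to a lesser degree, the event decrements in the cost-utility model.

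**Working it through.** The protocol gives no figure for this comparison, so there is none to reproduce. The check is whether the risk mix of cases differs from that of the pool from which controls are drawn.

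**Inputs** (Abstract and Sample size sections)
- DISTINCT-1: 3478 patients, VTE risk 0.75% in both arms.
- DISTINCT-2: 2500 patients, VTE risk 1.3%.
- DISTINCT-3: 2050 per arm, VTE risk 2.5% (control) and 1.25% (intervention).

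As a check on the inputs, the DISTINCT-1 size reproduces: 2 × 1565 = 3130, and 3130 / 0.9 = 3478. For DISTINCT-3 the pooled two-proportion formula gives 3696 before the interim and dropout allowances, against 3694 stated, which is close enough.

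**Expected VTE cases** = patients × risk
- DISTINCT-1: 3478 × 0.0075 = 26.1
- DISTINCT-2: 2500 × 0.013 = 32.5
- DISTINCT-3: 2050 × 0.025 + 2050 × 0.0125 = 76.9
- Total: 135.5

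**Mix by study**

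| | DISTINCT-1 | DISTINCT-2 | DISTINCT-3 |
|---|---|---|---|
| VTE cases | 19% | 24% | 57% |
| Non-cases | 35% | 25% | 40% |

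**Shift from the mix alone.** The documents give no quality-of-life level by risk group, so this step is an assumption. Let 1-year EQ-5D be lower by g in DISTINCT-3 than in DISTINCT-1, with DISTINCT-2 lower by g/2. With unrounded shares:

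shift = −g × (0.568 − 0.405) − (g/2) × (0.240 − 0.248) ≈ −0.159 g

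- g = 0.02: −0.003
- g = 0.05: −0.008
- g = 0.10: −0.016

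**With bleeding cases.** Assume major bleeding of 0.5% in DISTINCT-1, DISTINCT-2 and the DISTINCT-3 control arm. The 0.5% is the protocol's DISTINCT-3 control figure, carried over to the other two studies. The DISTINCT-3 intervention arm has 0.83%.
- Expected bleeds: 17.4 + 12.5 + 27.3 = 57.2, split 30% / 22% / 48%.
- Shift for bleeds alone: −0.003 to −0.006 for g = 0.05 to 0.10.
- VTE and bleeding together (192.6 events, 54% from DISTINCT-3, ignoring overlap): −0.006 to −0.013.

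No PJI rate is given, so the full case mix cannot be computed.

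All of these figures treat controls as a random draw from non-cases. Matching on age, sex, centre and surgery type may restore some balance. Differences in BMI or comorbidity within a study could add to the shift.

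**After the fix.** With matching on study, the DISTINCT-3 share of controls for VTE cases rises from about 40% to about 57%, and the between-study part of the shift is zero.

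**The case against.** The strongest reply is that the plan already deals with baseline where it matters most. The impact per event is estimated from differences that include the preoperative questionnaire, and a constant EQ-5D gap between risk groups cancels in a change from baseline. That stands, and it rules out a stronger reading that a reader might infer: that the QALY decrement ignores preoperative scores and carries the whole shift above. What remains for that estimate is any difference in trajectory between risk groups, which the documents do not let one size. The reply does not cover the separate 1-year comparison, for which no use of the preoperative value is stated, nor SF-36, which has no baseline.

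Second, the absence of a stated adjustment in a condensed article is not evidence that none is planned. The covariates are collected, and an analysis plan may well name them. That also stands, so the point rests on the matching list, which the article does state.

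Third, the shift is small. If the EQ-5D standard deviation were 0.2 (an assumption), 135 cases and 135 controls treated as independent would give a standard error of 0.2 × √(2/135) ≈ 0.024, larger than any shift computed here. That is fair. It limits the importance of the point, but a systematic error is not removed by being smaller than the random one.

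Fourth, surgery type is matched and appears in the TRiP(plasty) legend, and age may carry part of the risk. That also stands, so the figures for the mix may be too high.

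**Conclusion.** The point holds in a limited form. The matching list omits the variable by which the trial sorts patients on event risk, and the 1-year comparison is pooled over the resulting groups. On the protocol's rates the imbalance is clear: about 57% of VTE cases against about 40% of non-cases are in DISTINCT-3. Confounding of the 1-year OHS/OKS, SF-36 and EQ-5D comparison is therefore likely.

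It is not shown. A reader might infer that the estimates are certainly biased away from zero. The documents do not support that: they give no quality-of-life level by risk group, the weights in the score are not visible here, and existing matching may absorb some of the difference. The range of 0.008 to 0.016 for VTE cases depends on the assumed gap of 0.05 to 0.10 and on random selection of controls. It applies to EQ-5D levels, not to changes from baseline.

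The consequences are confined to a secondary outcome and, through trajectory differences only, to the cost-utility inputs. The randomised comparisons of VTE and major bleeding, and the event rates taken from them, are untouched. The change is worth making because it is cheap now and only partly recoverable later.

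**What to change.** - **Matching.** Add DISTINCT study, or a TRiP(plasty) risk band, to age, sex, study centre and type of surgery when 1-year controls are selected. A band is finer than study for DISTINCT-3, which has no upper limit on predicted risk.
- **Analysis.** State that the 1-year comparison is adjusted for predicted risk and, for EQ-5D and OHS/OKS, for the preoperative value of the same score. SF-36 can be adjusted for predicted risk only.
- **Controls already selected.** Keep them and rely on the adjustment.

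The cost is one more matching variable, using data already held. Controls are plentiful overall: in DISTINCT-3, about 4100 − 104 = 3996 patients without VTE or major bleeding for about 104 such events, or roughly 38 per case before PJI is counted. The downside is a somewhat narrower pool in small centres, where an exact match on every factor may occasionally be hard to find.

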### Sample size

#### Sample size calculation: DISTINCT-1 trial

By only including patients with a predicted VTE risk of <1.0%, a 3-month cumulative incidence of symptomatic VTE of 0.75% is expected in the control arm. This risk is based on the results from the development and validation studies of the TRiP(plasty) score.^18^ Multiple observational studies among patients in fast-track treatment protocols have shown that the risk of postoperative symptomatic VTE is ≤1% or even <0.5% with the use of in-hospital thromboprophylaxis only.^6 8 10 11^ Therefore, we expect no reduced or increased VTE risk when thromboprophylaxis is limited to in-hospital use only. Hence, the expected risk in the short-duration prophylaxis group is also 0.75%. The non-inferiority limit is set at 1%, which represents the minimal clinically important difference.^27^ Considering a one-sided alpha of 0.025 and a power of 90%, this leads to a necessary sample size of 3130 patients. To account for a maximum dropout rate of 10%, we aim to include 1739 patients in each group, totalling 3478 patients.

The incidence of (any) bleeding following THA/TKA has been reported to range from 0.5% to 3%. This variation is mainly caused by differences in bleeding definitions and the completeness and accuracy of patient follow-up.^12 13^ Hence, exact estimations of bleeding risks are difficult to obtain. Based on the available literature, we estimate that shortening the duration of thromboprophylaxis has no effect on major bleeding rates. The estimated relative reduced risk for minor bleeding+CRNMB is approximately 29%–50%.^10^,^1228 29^

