### Randomisation, blinding and treatment allocation

Approximately 2 weeks before surgery, patients will be randomised centrally by a clinical data management system (Castor Electronic Data Capture (EDC), V.2025.2.4.0 Amsterdam, the Netherlands). Randomisation within the DISTINCT-1 and DISTINCT-3 trials will be performed in a 1:1 ratio, using block randomisation with variable block sizes and stratified by study centre. This is an open-label study, meaning that patients and treating physicians will not be blinded to the intervention; however, outcome assessors will be. The DISTINCT-2 study is an observational study arm.

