### Analysis of primary endpoints

#### DISTINCT-1 statistics

A primary modified ITT analysis and a secondary PP analysis will be performed. The overall cumulative incidences of symptomatic VTE and major bleeding between the control and intervention groups will be compared, using a one-sided non-inferiority analysis for the absolute risk difference, with a significance level set as a one-sided p value of 0.025.

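### DISTINCT-1's 3130 evaluable patients do not deliver both 90% power and a one-sided alpha of 0.025; with a score-type test the fixed-sample power is about 85%, and lower if the interim stopping rule is binding

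*Protocol article*

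**What the plan says.** The section on the DISTINCT-1 sample size assumes that "a 3-month cumulative incidence of symptomatic VTE of 0.75% is expected in the control arm", and takes the same risk for the short-duration arm. It adds: "The non-inferiority limit is set at 1%, which represents the minimal clinically important difference". From these it concludes: "Considering a one-sided alpha of 0.025 and a power of 90%, this leads to a necessary sample size of 3130 patients". Enrolment is then inflated: "To account for a maximum dropout rate of 10%, we aim to include 1739 patients in each group, totalling 3478 patients".

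The DISTINCT-1 statistics section describes the primary comparison as "using a one-sided non-inferiority analysis for the absolute risk difference, with a significance level set as a one-sided p value of 0.025". It does not name the test statistic or the interval method.

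The section on interim analyses and patient safety sets looks at 25%, 50% and 75% of the target. DISTINCT-1 is to stop if the lower two-sided 95% confidence limit for VTE incidence in either arm lies above 0.75%. The DSMB reviews the interim results and advises the steering committee. The sample-size section does not mention this rule.

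**The concern.** The expected number of events per arm is 1565 × 0.0075 = 11.7. With so few events, the normal approximation to the risk difference is unreliable in the tail that decides non-inferiority. A sample size from that approximation meets its nominal 90% power only with a test that rejects too easily. A test that keeps the error at 2.5% falls short of 90%.

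This is the primary efficacy claim for limiting prophylaxis to the hospital stay. In a fixed-sample analysis at the planned risk, either false non-inferiority is about a fifth more likely than declared (3.03 / 2.5 = 1.21), or the chance of missing true non-inferiority is about 14.5% and not 10%.

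**Working it through.** **Inputs, all from the Protocol article.** VTE risk 0.75% in both arms; margin 0.01 on the risk difference; one-sided alpha 0.025; power 90%; 1:1 allocation; 10% dropout; endpoint at 90 days.

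**Step 1: reproduce the plan's figure.** Unpooled normal formula:

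n per arm = (z₀.₉₇₅ + z₀.₉₀)² × [p₁(1 − p₁) + p₂(1 − p₂)] / δ²

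= (1.960 + 1.282)² × (2 × 0.0075 × 0.9925) / 0.01²

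= 10.507 × 0.0148875 / 0.0001 = 1564.3, so 1565 per arm and 3130 in total.

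Dropout: 1565 / 0.90 = 1738.9, so 1739 per arm and 3478 in total. Both figures match the article.

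**Step 2: exact operating characteristics, fixed sample, 1565 per arm.** For each test, the probability of declaring non-inferiority is summed over two independent binomials. Error is taken at 1.75% (short) versus 0.75% (control), and power at 0.75% in both arms.

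| Test | One-sided error | Power |
|---|---|---|
| Wald (unpooled) | 3.03% | 89.8% |
| Agresti-Caffo | 2.67% | 88.4% |
| Likelihood ratio | 2.59% | 87.0% |
| Score (Farrington-Manning / Miettinen-Nurminen) | 2.32% | 85.5% |
| Newcombe | 2.32% | 85.5% |
| Continuity-corrected Wald | 2.09% | 85.2% |

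The pooled-variance test gives the same error and power as the unpooled Wald test. Wald error depends on the control risk: 3.4% at 0.5% versus 1.5%, and 2.9% at 1.0% versus 2.0%.

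**Step 3: is the shortfall only a matter of choosing a conservative test?** No. A Neyman-Pearson bound gives at most 86.8% power for any fixed-sample test that holds 0.025 at 1565 per arm.

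**Step 4: other sample sizes, fixed sample, score test.** With all 1739 per arm evaluable, power is 89.3%. Reaching 90% takes about 1790 evaluable per arm.

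**Step 5: add the interim stopping rule, treated as binding.** Looks are placed at 25%, 50% and 75% of 1565 per arm, and a stopped trial makes no non-inferiority claim. The article names no interim interval method, so three were tried.

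| Interim interval | Wald error, 1.75% v 0.75% | Wald error, 1.5% v 0.5% | Wald power | Score power |
|---|---|---|---|---|
| Clopper-Pearson | 2.0% | 3.2% | 86% | 81.5% |
| Wilson | 1.5% | 2.9% | 80% | 76.5% |
| Wald | 2.4% | 3.4% | 88% | 83.9% |

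With 1739 per arm the corresponding score-test powers are 83.9%, 77.3% and 88.0%. The rule costs power because its threshold, 0.75%, equals the planned risk, so either arm can cross it by chance when the planning assumptions are true.

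**The case against.** Four points can be made for the plan.

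- **The arithmetic is right.** It is: a standard formula gives exactly 3130. What is at issue is how well that formula works with about 12 events per arm.
- **The article commits to no Wald test, and an analysis plan that is not shown may name another.** This stands. A reader might infer that the trial will run at a true error of 3.0%, but the documents do not support that. No test is named, and leaving the choice to the analysis plan is ordinary practice. If the stopping rule is binding, even a Wald test has an error below 2.5% at 1.75% versus 0.75%. The point survives because the stated pair of alpha and power fails in a fixed-sample analysis whichever test is chosen. Under a binding rule, the power falls short of 90% even with a Wald test.
- **Fixed-sample figures ignore the stopping rule.** This also stands, and it is why 85% cannot simply replace 90%. The figure holds if the rule is advisory. If the rule binds, power is lower.
- **The loss is small and depends on the assumptions.** Partly right. The full fixed-sample shortfall needs the whole 10% dropout at a risk of exactly 0.75%. At 0.6% in both arms the fixed-sample score test has 91.2% power, and at 0.5% it has 94.4%. The article itself cites risks below 0.5% with in-hospital prophylaxis. But lower risks are also where the Wald error grows, so they do not rescue a Wald analysis.

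**Conclusion.** The concern holds in a limited form. The claim of 90% power at one-sided 0.025 with 3130 evaluable patients rests on a normal approximation that is too optimistic here, and the design does not deliver both figures.

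In a fixed-sample analysis the overstatement is about 4.5 points of power (90% against 85.5%) for a score or Newcombe analysis. For a Wald analysis it is about half a point of excess one-sided error at the planned risk, and more at lower control risks. If the stopping rule binds, score-test power is about 77–84%, and the Wald error still reaches about 2.9–3.4% at 1.5% versus 0.5%.

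These results assume independent binomial outcomes, no stratification, 1565 evaluable per arm and, for the last set, looks at exact quarters of that number. The finding concerns a stated operating characteristic. It does not show that the trial is too small to be useful or that its error rate will be inflated.

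**What to change.** In the DISTINCT-1 statistics section, specify an unstratified score-based (Miettinen-Nurminen) or Newcombe test and interval for the risk difference. Stratifying by centre is not part of this proposal: about 12 events per arm would be spread over at least 10 centres, and its behaviour was not examined.

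In the sample-size section, restate the power as about 85% with 3130 evaluable patients and about 89% if nobody drops out, and say that these are fixed-sample figures. State whether the interim stopping rule is binding and which interval it uses. If it is binding, also give the lower power computed with the rule.

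Keep the enrolment target of 3478. The change is to wording only; its cost is a less favourable stated power.
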